## Abstract

**Background:**

In Parkinson’s disease (PD), cognitive impairment is an important non-motor symptom heralding the development of dementia. Effective treatments to slow down the rate of cognitive decline in PD patients with mild cognitive impairment are lacking. Here, we describe the design of the Parkin’Play study, which assesses the effects of a cognitive health game intervention on cognition in PD.

**Methods/Design:**

This study is a multicentre, phase-II, open-randomized clinical trial that aims to recruit 222 PD patients with mild cognitive impairment. Eligible patients have PD, Hoehn & Yahr stages I–III, are aged between 40 and 75 years, and have cognitive impairment but no dementia. The intervention group (*n* = 111) will be trained using a web-based health game targeting multiple cognitive domains. The control group (*n* = 111) will be placed on a waiting list. In order to increase compliance the health game adapts to the subjects’ performance, is enjoyable, and can be played at home. From each group, 20 patients will undergo fMRI to test for potential functional brain changes underlying treatment. The primary outcome after 12 weeks of training is cognitive function, as assessed by a standard neuropsychological assessment battery and an online cognitive assessment. The neuropsychological assessment battery covers the following domains: executive function, memory, visual perception, visuoconstruction and language. A compound score for overall cognitive function will be calculated as the mean score of all test Z-scores based on the distribution of scores for both groups taken together. Secondary outcomes at follow-up visits up to 24 weeks include various motor and non-motor symptoms, compliance, and biological endpoints (fMRI).

**Discussion:**

This study aims at evaluating whether a cognitive intervention among PD patients leads to an increased cognitive performance on targeted domains. Strengths of this study are a unique web-based health game intervention, the large sample size, a control group without intervention and innovations designed to increase compliance.

**Trial registration:**

NTR5637 on 7-jan-2016

## Background

Non-motor symptoms in Parkinson’s disease (PD) are now recognized as major contributors to a decreased quality of life [1, 2]. Cognitive impairment is an important non-motor symptom and common in a substantial proportion of PD patients, even in early stages of the disease, and cognitive deficits typically worsen with disease progression [3]. Mild cognitive impairment in Parkinson’s disease (or PD-MCI) is an umbrella term that refers to the heterogeneity of cognitive deficits in multiple domains. It describes the transition from healthy aging to dementia in which cognitive dysfunction is present, but no functional impairment [4]. PD is considered to be a fronto-striatal syndrome that gives rise to cognitive deficits that are particularly apparent when patients need to generate behaviour on the basis of internal rather than external cues, and when they need to flexibly switch between well-learned tasks [5]. Salient cognitive deficits in PD thus usually relate to deficits in attention and executive function, yet the overall cognitive profile is heterogeneous, with co-existing deficits in memory and visuospatial functions also being frequent.

Current treatment strategies for the cognitive deficits are partially effective at best. Even with optimal medical management, cognitive impairment remains a common and incapacitating problem for many PD patients. Therefore, adequate strategies to improve cognitive function and to possibly delay the onset of PD dementia are urgently needed.

The aging brain is thought to retain some degree of plasticity [6], which suggests that older adults may benefit from cognitive training programs. Most studies on the effect of cognitive training programs have been performed in healthy older adults, or in people with cognitive impairment due to vascular pathology or traumatic brain injury. Results showed that these programs could improve multiple domains of cognition [7–9]. So far, only a few cognitive intervention-studies have been conducted in PD patients [10–12]. Some have shown that cognitive training programs improved memory performance [11] and overall cognitive functions [12] after only six weeks of training. Furthermore, cognitive training resulted in a reduced risk of developing PD-MCI at a one-year follow up assessment [12]. Indeed, a recent systematic review by Leung et al. [13] demonstrated a modest effect (g = 0.23, 95 % confidence interval 0.014–0.44, *p* = 0.037) of cognitive training on cognitive function in patients with mild to moderate PD. According to Leung et al. [13], studies in larger samples are needed to examine the abilities of a cognitive training in preventing cognitive decline in PD.

The functional changes in the brain and mechanisms responsible for the associated degeneration process of MCI are unknown [14]. However, several changes in functional connectivity between selective brain regions also take place during this degeneration process. Visualization of these changes helps to localize the responsible underlying mechanisms and may be used as a tool for evaluation of future treatments. In PD-MCI, changes in global patterns of resting-state functional connectivity have been associated with widespread connectivity decrements in several networks, including the default-mode network (DMN) and occipital networks [3, 15, 16]. Most studies demonstrated a pronounced working-memory related under-recruitment of the striatum and dorsolateral prefrontal regions, but also increments of the connectivity of the DMN with posterior cortical regions. The under-recruitment of the striatum may be associated with a reduced capacity for working-memory updating through a decreased phasic release of dopamine [17], but direct evidence linking cognitive changes to underlying brain mechanisms in PD is sparse. A longitudinal study that followed PD patients for three years mainly found functional connectivity changes in the parietal, temporal, and occipital cortices that were associated with cognitive decline [18]. No longitudinal studies have been published on functional network activity changes in PD patients during active cognitive training.

Here, we describe the design of the Parkin’Play study, a multi-centre randomized controlled trial (RCT) that examines the effect of a web-based gaming service (MyCognition AquaSnap) on cognitive function in PD patients with cognitive impairment but no dementia. The gaming service includes both a cognitive training videogame (AquaSnap) and a cognitive assessment (MyCQ™), which respectively trains and assesses the cognitive functions of a player on five core cognitive domains: attention, psychomotor speed, working memory, episodic memory, and executive function. The combination of these two components ensures an intervention adjusted to the (impaired) cognitive performance level of the subjects. Creating a web-based and adaptive health game that incorporates enhanced cognitive training loops may be more engaging, which may result in an increased compliance and effect in PD-MCI. The aim of this study is to determine whether a web-based gaming service designed for cognitive training is a feasible approach, and able to improve cognitive functioning within a three-month time frame in a new cohort of PD-MCI patients. We hypothesize that being able to train at home may optimize compliance to the intervention, as it motivates and rewards the patients.

### Objectives

The primary objective of the Parkin’Play study is to evaluate whether an individually tailored multi-domain cognitive intervention (a health game) leads to an improvement in cognitive performance on various targeted domains, such as executive function, memory, visual perception, visuo-construction, and language. The secondary objective is to study whether the effects persists over time, after the intervention has ceased.

Additionally, given the limited number of studies among PD-patients, it is still unclear whether cognitive improvement due to cognitive training has a neurobiological basis. To provide us with evidence for a mechanistic explanation for the effect of the intervention and to locate the changes in various brain structures, we will assess task-based and resting-state fMRI. Specifically, we will analyse changes in connectivity patterns in the resting-state sensorimotor network, including the supplementary motor area, sensorimotor cortex, and secondary somatosensory cortex [19].

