The second product is a custom-made and web-based cognitive training AquaSnap that was built with input from experts of both Radboud University Medical Center and Maastricht University Medical Center. The adaptive cognitive training aims at exercising the cognitive domains of attention, working memory, episodic memory, psychomotor speed and executive function. In AquaSnap, played online on a PC/laptop or Apple iPad, a player is required to explore the ocean in an underwater rover and complete specific tasks by taking pictures of fish. The pictures are worth currency, which can be used to dive deeper into the sea to discover different aquatic environments with rarer fish. The MyCQ™ assessment is carried out monthly and according to an individuals’ profile, AquaSnap adapts the speed and difficulty level of the game. The lower a player’s MyCQ™ score, the more training tasks they need to complete in that specific domain. Each cognitive domain is mainly trained by a particular training loop, while some domains are trained across different tasks (see Table 2). The game develops on different structural levels. At the basic structural level there are the loops, which corresponds to the five first tasks in Table 2. The loops are organized in underwater dives, in which the player undergoes a set of loops. At the Ocean map level, users have to organise their dive in order to both achieve the proposed mission and to discover new areas. The progress of the players on the map, and consequently the growth of difficulty in the training game depend on the coins the players are able to collect during their dives. In this way the game adapts its difficulty to the level of progression reached by the player (Fig. 2). Additionally, as mentioned above, the intensity of the training depends on the individual MyCQ™ scores, as the number of loops for each type of task depends on the score obtained on each cognitive domain. In this way, more impaired domains will receive more intensive training.

**Table 2 Tab2:** Individual tasks in AquaSnap and trained domains

	AquaSnap task	Description	Cognitive domain
1	Memory shot	Remember the position of the glowing fish in the loop	Working memory
2	Quick shot	Snap the fish as soon as you see it	Processing speed and attention
3	Careful quick shot	Snap the fish as soon as you see it, but be careful not to snap the shocking flash	Attention and executive function (inhibition)

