### Outcome measures

The primary outcome is global cognitive function, as assessed by both a standard neuropsychological assessment and the MyCQ™, at baseline and 12 weeks after baseline assessment. The standard neuropsychological assessment consists of various tests covering the following domains: executive function (Stroop Colour Word Test [28], category fluency and letter fluency in parallel versions [29]), memory (Rey Auditory Verbal Learning Test in parallel versions [30], Location Learning Test [31]), visual perception (Judgement of Line Orientation in parallel versions [32]), visuoconstruction (Rey-Osterrieth Complex Figure [33, 34]), and language (Boston Naming Test – Short Form). A compound score for overall (global) cognitive function will be calculated as the mean score of all test Z-scores based on the distribution of scores for both groups taken together. Z-scores of tests with higher scores representing worse performance will be inverted before computing the compound scores. By comparing Z-scores across different neuropsychological tests, the neuropsychological profiles of participants can be directly compared to identify the domains that benefitted most from the intervention.

The participants will also perform a monthly web-based online neuropsychological assessment (MyCQ™), which is part of the intervention program. Since the MyCQ™ is integrated in the AquaSnap health game (i.e., the difficulty level of the game automatically adapts according to MyCQ™ performance), it is not an independent measure of treatment effects, and hence the standard neuropsychological test battery is the primary outcome measure.

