### Statistical analysis procedure

Differences between the intervention and control group in global cognitive function (compound score of the neuropsychological test battery) at 12 weeks (primary endpoint) will be compared using independent sample t-tests. In addition, differences between groups in the individual cognitive domains will be tested using multivariate analysis of variance (MANOVA). Change in cognition over time (baseline, 12 weeks, 24 weeks) will be tested using repeated-measures ANOVA. All tests will be two-tailed with alpha set at 0.05. The assumptions of normality and homogeneity of variance will be assessed by inspection of normal probability plots and residual plots. In case assumptions are not met, appropriate data transformations will be used. Secondary outcomes will be presented as means, standard deviations, minimum, maximum, median, lower and upper quartiles. The number of observations and changes from baseline will be presented. Categorical data will be presented in contingency tables as frequencies and percentages. The analyses will be performed on an intention-to-treat basis. A secondary “Per-Protocol” analysis will also be included for the patients who have fully completed the study protocol for the primary endpoint. In order to investigate the effect of ‘missingness’, sensitivity analyses will be performed, including missing data augmentation using multiple imputation by chained equations [45] and maximum likelihood estimation with random effects.

For the main study, interim analysis will be conducted after 40 patients have completed the 12-week cognitive training period, including the corresponding assessments, to find out if the training is particularly beneficial or not. If, after interim analysis, it can be concluded that the training is particularly harmful, we may end the study and analyze the study data. This will only be decided in consultation with the local ethics committee.

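### Three of the domains that the primary objective calls targeted have no training task, so neither the global compound nor the MANOVA can by itself support a claim about targeted domains

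*Protocol article*

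**What the plan says.** The Objectives section states the primary aim as "improvement in cognitive performance on various targeted domains, such as executive function, memory, visual perception, visuo-construction, and language". The abstract's discussion and the opening of the Discussion section repeat the idea of targeted domains as the aim of the study.

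The description of the intervention gives a different list. The game aims at "exercising the cognitive domains of attention, working memory, episodic memory, psychomotor speed and executive function", and the Background says the gaming service trains and assesses "five core cognitive domains: attention, psychomotor speed, working memory, episodic memory, and executive function". Table 2 assigns each of the seven game tasks to one or more of these.

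Under Outcome measures the independent battery contains "executive function (Stroop Colour Word Test [28], category fluency and letter fluency in parallel versions [29"). It adds two tests of memory (one of verbal learning, one of location learning) and a line-orientation test for visual perception. The remaining two tests are given as "visuoconstruction (Rey-Osterrieth Complex Figure [33, 34]), and language (Boston Naming Test – Short Form"). The primary compound is the plain mean of all test Z-scores. The same section says that comparing Z-scores across tests will serve "to identify the domains that benefitted most from the intervention". The Statistical analysis procedure states that "differences between groups in the individual cognitive domains will be tested using multivariate analysis of variance (MANOVA").

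**The concern.** The objective lists the domains of the outcome battery as if they were the domains of the intervention. Three of the five have no training task, and three trained domains (attention, psychomotor speed, working memory) are not named domains of the battery. The online assessment does measure those three, but Outcome measures says it is not independent of the game.

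Two consequences follow. First, the global compound mixes tests from trained and untrained domains, so a difference on it does not show that the targeted functions improved. A positive result could be reported as benefit in domains that the game never addressed. Second, the protocol wants to say which domains gained most, yet the one inferential method it names for domains returns a single joint test.

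A further question is how much the tests from untrained domains could weaken the signal on the primary outcome. The power section sets its effect size on the compound without discussing them.

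**Working it through.** **Step 1. Domain lists side by side.**

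| Domain | Called targeted in Objectives | Task in Table 2 | Named tests in battery |
|---|---|---|---|
| Executive function | yes | yes | 3 (Stroop, category fluency, letter fluency) |
| Memory | yes | yes (episodic; working) | 2 (Rey verbal learning, location learning) |
| Visual perception | yes | none | 1 (line orientation) |
| Visuoconstruction | yes | none | 1 (complex figure) |
| Language | yes | none | 1 (naming) |
| Attention | no | yes | not a named domain |
| Psychomotor speed | no | yes | not a named domain |

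Working memory is trained but is not separately named in the battery. The overlap is executive function and memory, with 3 + 2 = 5 of 8 named tests. The other 3 of 8 come from domains with no training task.

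**Step 2. The protocol's own figure.** Power and sample size estimate gives d = 0.4 on the compound, power 0.8, two-sided alpha 0.05 and 1:1 allocation. The normal approximation is 2 × (1.960 + 0.842)² / 0.4² = 98.1, so 99 per arm and 198 in total. The t-test needs 99.08, so 100 per arm and 200 in total, as stated; power at 100 per arm is 80.4%. For 10% attrition, 200 / 0.9 = 222.2, which agrees with the stated 222 apart from rounding. The arithmetic stands.

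**Step 3. Scenario for the compound.** These assumptions are not in the document: one score per named test, a common inter-test correlation r of 0.2 to 0.5, the same gain δ (in SD units) on each of the five tests, and no gain on the other three.

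- SD of a mean of m Z-scores: SD(m) = √[(1 + (m − 1)r) / m]
- Trained-domain compound: d = δ / SD(5)
- Global compound: d = (5/8)δ / SD(8)
- Ratio of global to trained-domain effect: (5/8) × SD(5) / SD(8)

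Example at r = 0.2: SD(5) = √(1.8/5) = 0.600 and SD(8) = √(2.4/8) = 0.548. The ratio is 0.625 × 0.600 / 0.548 = 0.685.

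In scenario A the trained-domain compound has d = 0.4. In scenario B each of the five tests gains 0.4 SD. Power is for a two-sided t-test at 100 per arm.

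| r | Ratio | A: global d | A: power | B: global d | B: power | Trained-domain d needed for global 0.4 |
|---|---|---|---|---|---|---|
| 0.2 | 0.685 | 0.27 | 49% | 0.46 | 90% | 0.58 |
| 0.3 | 0.666 | 0.27 | 47% | 0.40 | 81% | 0.60 |
| 0.4 | 0.654 | 0.26 | 45% | 0.36 | 72% | 0.61 |
| 0.5 | 0.645 | 0.26 | 44% | 0.33 | 65% | 0.62 |

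The two scenarios differ only in where 0.4 is placed. Scenario A implies a gain per trained test of 0.4 × SD(5), which is 0.24 SD at r = 0.2 and 0.31 SD at r = 0.5.

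**Step 4. The domain analysis.** A two-group MANOVA on five domain scores tests whether the two mean vectors are equal. Rejection says that they differ somewhere. It gives neither the domain nor the size of the difference. The comparison of Z-scores in Outcome measures could describe a profile, but no inferential form is given for it.

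**The case against.** The strongest reply is that a broad, independent battery is a sound choice when the primary outcome is defined as global cognitive function. Executive function and memory appear in both lists and supply most of the tests, so the objective and the game are far from unrelated. This stands, and it is why the global compound should stay primary.

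A reader might infer that the trial has under 50% power. The documents do not support that. The power section places d = 0.4 on the compound itself, already reduced from 0.78 on a single test in the source study. Scenario A moves 0.4 to a different score and assumes exactly zero transfer, which nothing in the protocol establishes. The trained-domain effect needed for 0.4 globally, 0.58 to 0.62, is below that 0.78. The number of scores per test is also not stated.

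A reader might also infer that a null result could not be told apart from lack of transfer. That goes too far. The online assessment covers the five trained domains monthly in both arms, although it is not independent, and the domain analysis separates executive function and memory from the rest.

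It is also tempting to say that the MANOVA cannot show domain effects, or that uncorrected follow-up tests are planned. The protocol describes no such follow-ups. They and their multiplicity control may sit in an analysis plan that is not shown. What remains is narrower: the omnibus test, as named, does not locate the effect.

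**Conclusion.** The concern holds in limited form. The Objectives section contradicts the description of the game for three of its five named domains, and this rests on the text alone. It follows that the primary comparison cannot by itself carry a claim about targeted domains, and that the MANOVA does not by itself deliver the domain ranking that Outcome measures promises.

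The dilution figures show what is possible and are not a property of the plan. Under the stated assumptions power on the global compound ranges from 44 to 49% in scenario A and from 90 to 65% in scenario B; partial transfer to the other three tests would raise both. They do not call for a change to the sample size. They do show why a separate estimate for the trained domains is worth having.

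**What to change.** 1. Reconcile the list of targeted domains in Objectives, and the matching statements in the abstract and Discussion, with Table 2, so that trained and untrained domains are told apart.
2. Keep the global compound as the primary outcome.
3. Pre-specify a compound of the five executive and memory tests as a ranked secondary outcome, with its estimate and 95% confidence interval. Base any statement about targeted domains on it.
4. In place of the MANOVA, report the baseline-adjusted group difference for each of the five battery domains, with confidence intervals and Holm-adjusted p-values.

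The cost is some rewording and a few more analysis lines on data already collected, with no new visits or patients. The downside is one more secondary outcome and a narrower claim.

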### Study design

The Parkin’Play study is a multicenter phase-II open-randomized controlled study that aims to recruit 222 patients with Parkinson’s disease with PD-MCI. Patients are randomly assigned to the intervention (cognitive training) or the control group (waiting list). All participants will undergo three assessments (t = 0, t = 1, and t = 2), which consist of neuropsychological assessments and questionnaires. In 20 patients from each group (total *n* = 40) two fMRI scans will be obtained (t = 0 and t = 1). The duration of the main intervention will be 12 weeks. In order to investigate the compliance and attractiveness of the health game, patients will be given the opportunity to continue playing for an additional 12 weeks (Fig. 1). The study will be analysed based on an intention-to-treat approach and results will be published on behalf of the Parkin’Play investigators.

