### Intervention

The total duration of the intervention will be 12 weeks for both groups, with a voluntary extension of the cognitive training for an additional 12 weeks.

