#### Waiting list (control group)

The control group is designed as a waiting list group in order to increase compliance. The participants are required to perform the MyCQ™ assessment monthly. For motivational purposes, the control group is offered to take part in a deferred intervention after 12 weeks (e.g. from week 12 until 24), with the same intensity as the intervention group in the first 12 weeks.

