### Study activities

Enrolment will take place in the weeks prior to baseline assessment, except for the additional inclusion assessments (see Table 4). The following demographics and general variables are collected at baseline: date of birth, sex, educational level, age at onset, disease duration, and details on Parkinson medication (i.e., drug name, dose, frequency, levodopa equivalence). Details on Parkinson medication will also be collected at both follow-up measurements. Randomization will be performed after the baseline assessment. Primary and additional outcome assessments will be performed at baseline, after 12 and after 24 weeks follow up. The additional fMRI scans will be performed at baseline and after 12 weeks, matching the primary outcome assessments. The intervention group will be required to play the health game from start of the intervention until week 12 for at least 36 sessions of 30 min (three times a week). After week 12, both the intervention as well as the control group will be allowed to continue playing the health game free of choice. All patients will be examined in their on-state.

**Table 4 Tab4:** Study schedule and assessments

	Timepoint →	-*t* _1_	*t* _0_			*t* _1_	*t* _2_
	Visit # →	0	1			2	3
	Week # →	-1 to -3	0	4	8	12	24
ENROLMENT: Screening & inclusion assessments							
Regular clinical intake		X					
Demographics		X					
Inclusion/exclusion		X					
National Adult Reading Task			X				
Montreal Cognitive Assessment			X				
Epworth Sleepiness			X				
Levodopa equivalent dose (LED)			X			X	X
ASSESSMENTS: Primary outcomes							
Standard neuropsychological battery			X			X	X
MyCQ™ assessment			X	X	X	X	X
Additional outcomes							
Motor function (UPDRS part III)			X			X	X
Self-report questionnaires			X			X	X
Parkinson Disease Questionnaire-39			X			X	X
Pre-Rasch-built Overall Disability Scale			X			X	X
fMRI exclusion criteria		X					
fMRI scan			X			X	
INTERVENTIONS							
Randomization			X				
Game playing (36 sessions of 30 min)			X	X	X	*X*	*X*

Only for subset of patients (*n* = 40)

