## Discussion

The overall aim of this phase-2 multi-center open-randomized controlled clinical trial among PD patients is to evaluate whether a web-based health game designed to train cognition leads to an improvement in cognitive performance on targeted cognitive domains, relative to a control group on a waiting list. The strengths of the Parkin’Play study are the large sample size (*n* = 222), the gamified and home-based training approach, the individually tailored and adaptive training, and the application of fMRI assessments in order to explore underlying brain mechanisms. The addition of the 24-week follow up assessment provides valuable information about maintenance of benefit and about the feasibility of implementing health games in a PD population.

Now that the new MDS-criteria for PD-MCI have been introduced, this study will for the first time study a large sample of patients fulfilling the proposed criteria in a clinical trial [13]. Previous cognitive clinical trials for PD have incorporated a range of cognitive and functional outcome measures, partly based on scales derived from Alzheimer’s disease [51, 52]. This illustrates the lack of consensus on cognitive outcome measures. Furthermore, regulatory agencies may require measures that take into account a functional benefit for the patient. In this study, a compound score from a neuropsychological test battery will be used and complemented with the MyCQ™. The recently validated PD-CFRS scale was chosen to study functional benefit with demonstrated responsiveness over time [53].

The Parkin’Play intervention consists of various innovations. Firstly, performing cognitive training at home is likely to optimize compliance, since PD patients’ reduced mobility might prevent them from attending outdoor activities [12, 47]. Secondly, a task that is too hard may result in anxiety and therefore lead to resistance of collaboration to the treatment (e.g. stop playing the health game). The health game and MyCQ™ assessment combination adapts to the subject’s capabilities and thereby results in a challenging game specifically tailored to the individual. Thirdly, the health game aims at being fun to play, introducing a multi-layer game story opposed to abstract repetitive cognitive brain trainings. These innovations are aimed at increasing the compliance of the intervention and prevent substantial attrition rates associated with study failures.

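### The randomised week-24 comparison cannot show whether the effect persists after training stops, because both arms may play the game between weeks 12 and 24

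*Protocol article*

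**What the plan says.** The Objectives section sets the secondary aim: "The secondary objective is to study whether the effects persists over time, after the intervention has ceased".

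The design sections then describe weeks 12 to 24 as follows.

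- **Intervention arm.** Under Study design, "patients will be given the opportunity to continue playing for an additional 12 weeks". The Intervention section describes the 12-week programme "with a voluntary extension of the cognitive training for an additional 12 weeks". The Compliance section says that this continued play will be tracked.
- **Control arm.** Under Waiting list (control group), "the control group is offered to take part in a deferred intervention after 12 weeks (e.g. from week 12 until 24"), and this is to be "with the same intensity as the intervention group in the first 12 weeks".
- **Both arms.** Under Study activities, "After week 12, both the intervention as well as the control group will be allowed to continue playing the health game free of choice".

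The neuropsychological battery is given at baseline, week 12 and week 24 (Table 4). For the analysis, the Statistical analysis procedure says "Change in cognition over time (baseline, 12 weeks, 24 weeks) will be tested using repeated-measures ANOVA", on an intention-to-treat basis. The Discussion then claims: "The addition of the 24-week follow up assessment provides valuable information about maintenance of benefit".

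**The concern.** To test persistence after training stops by a randomised comparison, two things are needed: a period in which the trained arm has stopped, and a comparator that is still untrained. The document secures neither after week 12, yet it names persistence as an objective and says that the week-24 visit informs it.

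The error can run in both directions. If the benefit lasts and the deferred game also works, the arms converge, and the result could be taken as a lost effect. If intervention patients stay ahead because they kept playing, continued training could be taken as persistence.

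A smaller matter bears on the same contrast. One section describes the controls' deferred training as matching the intensity of the first 12 weeks in the intervention arm. Another leaves play after week 12 to each patient's choice. What a week-24 difference means depends on which description applies.

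**Working it through.** **Inputs from the protocol article (Power and sample size estimate).** Cohen's d = 0.4, two-sided alpha 0.05, power 0.80, 1:1 allocation, 200 evaluable patients, 10% attrition, 222 recruited.

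**Assumptions (not in the documents).**
- r: share of the week-12 effect present in the intervention arm at week 24, whether retained or topped up by further play.
- u: share of the full effect that controls gain on average from deferred play.
- rho: correlation between visits, taken as equal for all pairs.

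**1. The plan's own figure.** The normal approximation gives n per arm = 2 × (1.96 + 0.84)² / 0.4² ≈ 98.1, so 99. The t-based solution is 99.08, so 100 per arm and 200 in total. Then 200 / 0.9 = 222.2, against 222 stated. The sample size reproduces and is not at fault.

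**2. Week-24 difference between arms.** In standard deviation units,

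d24 = 0.4 × (r − u).

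Different truths give the same value:

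| Truth | r | u | d24 |
|---|---|---|---|
| Full persistence, full control catch-up | 1 | 1 | 0 |
| Complete loss, no control uptake | 0 | 0 | 0 |
| Full persistence, half catch-up | 1 | 0.5 | 0.20 |
| Half lost, no control uptake | 0.5 | 0 | 0.20 |

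One observed difference cannot be split into r and u, and more patients would not change that. Moreover, r itself mixes retention with continued training.

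**3. Size under full retention (r = 1).** Two-sample t-test, 100 per arm, noncentrality d24 × √(100/2):

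| Average control gain u | d24 | Noncentrality | Power |
|---|---|---|---|
| 0% | 0.40 | 2.83 | 0.80 |
| 25% | 0.30 | 2.12 | 0.56 |
| 50% | 0.20 | 1.41 | 0.29 |
| 75% | 0.10 | 0.71 | 0.11 |
| 100% | 0 | 0 | 0.05 |

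**4. Omnibus group-by-time test over weeks 0, 12 and 24.** With n per arm and unit variance, the noncentrality is (n/2) × Σ(d_t − mean d)² / (1 − rho).

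- Group differences (0, 0.4, 0.4): mean 0.267; sum of squares 0.0711 + 0.0178 + 0.0178 = 0.1067.
- Group differences (0, 0.4, 0): mean 0.133; sum of squares 0.0178 + 0.0711 + 0.0178 = 0.1067.

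The two are equal, so noncentrality and power are equal at any rho:

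| rho | Noncentrality, both patterns | Power, both patterns |
|---|---|---|
| 0.75 | 50 × 0.1067 / 0.25 = 21.3 | 0.99 |
| 0.5 | 50 × 0.1067 / 0.5 = 10.7 | 0.84 |
| 0.3 | 50 × 0.1067 / 0.7 = 7.6 | 0.69 |

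A significant interaction therefore looks the same whether the week-12 difference is still there at week 24 or has vanished.

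**The case against.** The strongest reply is that play after week 12 is optional in both arms and playing time is recorded automatically (Cognitive training section). Some intervention patients may stop, and their change from week 12 to 24 would bear on persistence. This stands as far as it goes. A reader might infer that the objective cannot be addressed at all, or that no control stays untrained; the documents do not support either, because the game is offered and not imposed. But those who stop choose to do so, untrained controls at week 24 are not assured, and the article describes no analysis by playing time after week 12. A separate analysis plan could add one, but it could not restore a randomised untrained comparator.

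A reader might also infer a loss of power in the repeated-measures analysis. At a visit correlation of 0.75, power for a group main effect over three visits falls from 54% without control gain to 18% with full control gain. The arithmetic is right, but the article does not name that test, and the group-by-time test loses no power between the two patterns above. The fault is one of identification.

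Nor is 5% power at week 24 the expected case. It needs controls to gain the full effect on average, and the documents give no uptake. The article also states no rule by which a null result at week 24 would be declared a loss of effect.

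The two descriptions of control play can be partly harmonised: one may describe the programme on offer, the other the freedom to take it up. The wording still needs clarifying, but it is not a flat contradiction.

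Finally, week 24 keeps its use for feasibility and continued use (Compliance section), and its between-arm contrast is a valid randomised comparison of early with deferred access.

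**Conclusion.** The point holds for the randomised comparison. As designed, the week-24 difference between arms cannot establish persistence after training stops, and it does not support the Discussion's statement on maintenance. This follows from the text alone. The power range of 0.80 down to 0.05 illustrates the size and rests on d = 0.4, 100 per arm, full retention and assumed control gains of 0 to 100%. The equality of the two interaction patterns does not depend on the visit correlation.

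A reader might infer that the trial's main result is at risk. It is not: the primary comparison is at week 12, before controls are offered the game, and the sample size for the compound score reproduces. This is a moderate issue on a secondary objective.

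**What to change.** 1. Keep week 12 as the only randomised comparison of training with no training.
2. Label any week-24 between-arm contrast as early versus deferred access, and do not read it, or the omnibus group-by-time test over three visits, as evidence for or against persistence.
3. Restate the secondary objective as exploratory and non-randomised. In the intervention arm, report the change from week 12 to 24 with a 95% confidence interval, by logged playing time after week 12. In the control arm, report the change over weeks 12 to 24 against that over weeks 0 to 12. State that neither estimates persistence against no training.
4. Qualify or remove the maintenance statement in the Discussion.
5. Reconcile the Waiting list and Study activities sections on what controls do after week 12.

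The cost is rewording of the objective, analysis and discussion text. No new patients, visits or data are needed. The price is a weaker claim about durability.
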